# Evaluation the Effect of Ascorbic Acid compared to normal saline on the hidden blood loss in total knee arthroplasty

More options ▼

## Protocol summary

|                                                      |                                                                                                                                                                                                                                                                                                                                                                                                                                                                                                      |
|------------------------------------------------------|------------------------------------------------------------------------------------------------------------------------------------------------------------------------------------------------------------------------------------------------------------------------------------------------------------------------------------------------------------------------------------------------------------------------------------------------------------------------------------------------------|
| Study aim                                     | In this study we are aiming to investigate the effect of the antioxidant agent including ascorbic acid on the amount of hidden blood loss in total knee arthroplasty (TKA).                                                                                                                                                                                                                                                                                                                          |
| Design                                        | A double-blind randomized controlled trial with two parallel groups                                                                                                                                                                                                                                                                                                                                                                                                                                  |
| Settings and conduct                          | In this randomized controlled clinical trial, 100 patients which are scheduled for TKA will be consecutively assigned into two groups in a 1:1 ratio. The patients in group A will receive three doses of ascorbic acid. The patients in group B will receive only normal saline as a control group. In this double-blind study, patients and data collectors are blinded and unaware of the patient's assigned group. Informed consent will be obtained from all the patients prior to the surgery. |
| Participants/Inclusion and exclusion criteria | Inclusion criterion: patients who are scheduled for total knee arthroplasty. Non-inclusion criteria: history of thromboembolic events like deep vein thrombosis or pulmonary embolism; a history of cardiovascular disease; clotting disorders including abnormal PT, PTT or INR; being in pregnancy or in the lactation period; drug abusers or alcoholics; severe renal dysfunction; severe infection; the preoperative hemoglobin <10 g/dL; diagnosis of inflammatory arthritis                   |
| Intervention groups                           | Intervention group: patients in this group will receive the first ascorbic acid dose (1 g in 10 mL) at the beginning of the surgery. Another dose of ascorbic acid (1 g in 10 mL) will be infused during the surgery. After the surgery, an additional dose of ascorbic acid (1 g in 10 mL) will be infused during the first 12 hour postoperative period. Control group: The patients in this group will receive only normal saline.                                                                |

## General information

| Reason for update                      |                                                                                                                                                                                                                                                                                                  |
|----------------------------------------|--------------------------------------------------------------------------------------------------------------------------------------------------------------------------------------------------------------------------------------------------------------------------------------------------|
| Acronym                                |                                                                                                                                                                                                                                                                                                  |
| IRCT registration information   | IRCT registration number: IRCT20221104056393N1
Registration date: 2023-06-27, 1402/04/06
Registration timing: registered_while_recruiting
Last update: 2023-06-27, 1402/04/06
Update count: 0                                                     |
| Registration date               | 2023-06-27, 1402/04/06                                                                                                                                                                                                                                                                           |
| Registrant information          | 
 Name
           [name]
 Name of organization / entity
 Country
           Iran (Islamic Republic of)
 Phone
           [contact]
 Email address
           [contact]         
 |
| Recruitment status              | Recruitment complete                                                                                                                                                                                                                                                                      |
| Funding source                  |                                                                                                                                                                                                                                                                                                  |
| Expected recruitment start date | 2023-06-18, 1402/03/28                                                                                                                                                                                                                                                                           |
| Expected recruitment end date   | 2023-06-29, 1402/04/08                                                                                                                                                                                                                                                                           |
| Actual recruitment start date   | empty                                                                                                                                                                                                                                                                                     |
| Actual recruitment end date     | empty                                                                                                                                                                                                                                                                                     |
| Trial completion date           | empty                                                                                                                                                                                                                                                                                     |
| Scientific title                | Evaluation the Effect of Ascorbic Acid compared to normal saline on the hidden blood loss in total knee arthroplasty                                                                                                                                                                             |

|                                               |                                                                                                                                                                                                                                                                                                                                                                                                                                                                                                                                                                                                                                                                                                 |
|-----------------------------------------------|-------------------------------------------------------------------------------------------------------------------------------------------------------------------------------------------------------------------------------------------------------------------------------------------------------------------------------------------------------------------------------------------------------------------------------------------------------------------------------------------------------------------------------------------------------------------------------------------------------------------------------------------------------------------------------------------------|
| Public title                           | The Effect of Ascorbic Acid on the blood loss in Total Knee Arthroplasty                                                                                                                                                                                                                                                                                                                                                                                                                                                                                                                                                                                                                        |
| Purpose                                | Treatment                                                                                                                                                                                                                                                                                                                                                                                                                                                                                                                                                                                                                                                                                       |
| Inclusion/Exclusion criteria           | 
Inclusion criteria:
Candidates of total knee arthroplasty patients who provide written informed consent to be included in this study
 
Exclusion criteria:
history of thromboembolic events like deep vein thrombosis or pulmonary embolism history of cardiovascular disease like myocardial infarction or atrial fibrillation being in pregnancy or in the lactation period drug abusers or alcoholics severe renal dysfunction severe infection the preoperative hemoglobin less than 10 g/dL diagnosis of inflammatory arthritis like rheumatoid arthritis, pigmented villonodular synovitis and etc clotting disorders including abnormal PT, PTT or INR
 |
| Age                                    | No age limit                                                                                                                                                                                                                                                                                                                                                                                                                                                                                                                                                                                                                                                                                    |
| Gender                                 | Both                                                                                                                                                                                                                                                                                                                                                                                                                                                                                                                                                                                                                                                                                            |
| Phase                                  | N/A                                                                                                                                                                                                                                                                                                                                                                                                                                                                                                                                                                                                                                                                                             |
| Groups that have been masked           | 
 
• Participant
 
• Outcome assessor
 
                                                                                                                                                                                                                                                                                                                                                                                                                                                                                                                                                                                                     |
| Sample size                            | Target sample size: 100                                                                                                                                                                                                                                                                                                                                                                                                                                                                                                                                                                                                                                                                  |
| Randomization (investigator's opinion) | Randomized                                                                                                                                                                                                                                                                                                                                                                                                                                                                                                                                                                                                                                                                                      |
| Randomization description              | In this randomized controlled clinical trial, the patients will be consecutively and alternately (one in between) assigned into two groups in a 1:1 ratio.                                                                                                                                                                                                                                                                                                                                                                                                                                                                                                                                      |
| Blinding (investigator's opinion)      | Double blinded                                                                                                                                                                                                                                                                                                                                                                                                                                                                                                                                                                                                                                                                                  |
| Blinding description                   | 
In this double-blind study, patients and the data collector are blinded. Patients are kept unaware of their group assignment and the intervention they are receiving. Patients in both groups receive serums with covers so that the content will not be visible to the patients. Both the treatment and control groups receive identical instructions and support. The data collector is kept blind to the group assignment of each patient. Collecting data including laboratory values after the surgery and clinical examinations will be performed without knowing the
                                                                                                              |

intervention done for the patient and only according to their records number.

|                   |          |
|-------------------|----------|
| Placebo    | Not used |
| Assignment | Parallel |

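### The trial is labelled randomized, but the only assignment method it states is alternation, which is deterministic and has no described concealment

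*Protocol*

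**What the plan says.** The Protocol summary (Design) describes "A double-blind randomized controlled trial with two parallel groups". The next entry, Settings and conduct, again calls the trial randomized and says that the patients "will be consecutively assigned into two groups in a 1:1 ratio", without naming a random element.

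In General information, the randomization field is marked as randomized. The Randomization description beside it gives the method: "the patients will be consecutively and alternately (one in between) assigned into two groups in a 1:1 ratio". The sample size entry reads "Target sample size: 100", which at 1:1 means 50 per group.

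On masking, the list of masked groups in General information names the participant and the outcome assessor. The Blinding description says: "In this double-blind study, patients and the data collector are blinded". It adds that "Patients in both groups receive serums with covers so that the content will not be visible to the patients", and that postoperative data are collected without knowledge of the intervention and "only according to their records number".

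General information also marks recruitment as complete. The same table gives the registration timing as during recruitment and leaves the actual recruitment dates empty.

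**The concern.** The label and the method contradict each other. This is not a detail left to a statistical analysis plan: the method is stated, and it is not randomization. Once the starting arm is fixed, alternation leaves nothing to chance.

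The practical consequence is predictability at the point of enrolment. Someone who knows the previous patient's arm and the order of entry knows the next arm before deciding whether to approach, defer or exclude a patient. There is room for such decisions. Several exclusion criteria are judgements without thresholds (for example, severe renal dysfunction and severe infection). Preoperative haemoglobin is screened at entry, and it is also the starting point of the primary outcome measure, haemoglobin drop.

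At stake are the protection against selection bias, the randomization basis for the p-value and confidence interval, and the correct classification of the trial by readers and evidence reviewers.

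**Working it through.** **1. Label against method.**

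| Place in the Protocol | Label | Method stated |
|---|---|---|
| Protocol summary, Design | randomized | none |
| Protocol summary, Settings and conduct | randomized | consecutive assignment, 1:1 |
| General information, Randomization description | randomized | consecutive and alternate assignment, 1:1 |

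No section shown gives a random sequence, a generator, a list or a concealment step.

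**2. How predictable is the next assignment?** Input from the document: N = 100 at 1:1.

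- Possible sequences under alternation: 2, or 1 once the starting arm is known.
- Possible balanced random sequences: C(100, 50) ≈ 1.01 × 10^29.

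The table gives the expected number of correct guesses for someone who knows all past assignments and always picks the likelier arm. The block sizes are illustrative assumptions.

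| Scheme | Correct guesses of 100 |
|---|---|
| Alternation, first arm a coin toss | 99.5 (all 99 after the first) |
| Permuted blocks of 4, size known | 70.8 |
| Permuted blocks of 10, size known | 65.3 |
| One random 50/50 list | 55.8 |
| Simple randomization | 50 |

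**3. What could steering do?** The document gives no figure for this, so the inputs are assumptions:

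- q = share of patients steered, better prognosis to active and worse to control: 10%, 20%, 30%.
- rho = correlation of the prognostic score with the outcome: 0.3, 0.5.
- No true effect, a normal outcome with SD 1, and a two-sided test at 5%.

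Formulas:

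- SE of the difference = sqrt(2/50) = 0.20 SD.
- Bias = q × rho × k, where k is the prognostic difference between arms, in SD, among the steered patients.
- Type I error = Φ(−1.96 + bias/SE) + Φ(−1.96 − bias/SE).

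Two values of k cover two ways of steering:

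- Perfect sorting at the median, as if patients were passed over until a suitable one appeared: k = 2 × sqrt(2/π) = 1.596.
- Swapping two neighbours in the order, so that the better of the pair goes to active: k = 2/sqrt(π) = 1.128.

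| Mechanism | rho | q = 10% | q = 20% | q = 30% |
|---|---|---|---|---|
| Median sorting | 0.5 | 6.8% | 12.6% | 22.3% |
| Median sorting | 0.3 | 5.7% | 7.7% | 11.1% |
| Neighbour swap | 0.5 | 5.9% | 8.7% | 13.5% |

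Worked case, median sorting, rho = 0.5, q = 20%: bias = 0.20 × 0.5 × 1.596 = 0.160 SD; bias/SE = 0.80; Φ(−1.16) + Φ(−2.76) ≈ 0.126.

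With q = 0 the bias is zero and the error stays at 5%.

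**The case against.** The strongest reply is that alternation alone biases nothing: without steering, step 3 shows no inflation. The document does not say who enrols, who assigns or who knows the order, and a person unaware of all earlier arms could not predict the next. That stands. A reader might infer that every enroller knew every next arm, or that selection bias took place. The document supports neither. It supports only that the sequence is predictable to anyone with one earlier assignment and the order, and that no safeguard at enrolment is described.

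A reader might also infer that the trial cannot be called double-blind. That goes too far. The protocol defines its masking as participant plus outcome assessor, with covered serums and data collection without knowledge of the intervention. Alternation puts this at risk, because one disclosed arm reveals the others to anyone who has the order, but it does not cancel the masking. Nor can one conclude that the data collector could read the arm from the record number. The document does not say how these numbers are issued, and they may be ordinary hospital numbers.

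It is fair, too, that the larger error rates assume error-free sorting at the median and that neither q nor rho comes from the document. The neighbour-swap row gives the milder case.

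None of this touches the contradiction between label and method. Masking after assignment does not protect the decision to enrol or the order of enrolment.

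**Conclusion.** The point holds and should be corrected. The document calls the trial randomized in the Design entry, in Settings and conduct, and in the randomization field, while the only method it states is deterministic alternation without described concealment. This rests on the text alone and needs no assumption.

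The size of any bias is unknown. Under the stated assumptions, type I error runs from about 6% to 22% with median sorting, and from about 6% to 13.5% at correlation 0.5 with neighbour swaps. These figures show what the design leaves open, not what happened.

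**What to change.** First establish whether any patients remain to be enrolled, and which method was actually used.

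- **If patients remain:** replace the Randomization description with wording such as: *Assignment follows a computer-generated 1:1 list in randomly permuted blocks of varying size, prepared by a person not involved in enrolment. Each assignment is concealed until consent has been given and the patient has been entered.* The cost is one list, a concealment procedure and an amendment. It cannot repair assignments already made.
- **If recruitment is complete and alternation was used:** replace the randomized label in the Design entry, in Settings and conduct, in the randomization field and in all reports with *alternately allocated (quasi-randomised)*. The titles do not use the word and need no change. State who knew the sequence, and report eligible patients not enrolled and baseline comparability, including preoperative haemoglobin. An analysis adjusted for preoperative haemoglobin, which is already measured, may be added as support. It does not restore a randomization basis and cannot correct steering on unmeasured factors. The cost is a change of wording and some extra reporting.

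The downside of relabelling is a weaker but correct design label.
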